| To estimate the rates of compliance with follow up for women who test HPV positive on a self-sample | *Attendance at follow up (conventional cervical screening test or colposcopy) within 6                                                                                                                                                                                                                                                     | 
Number of women who test HPV positive on a self-sample and
 
(i) have a conventional cervical screening test recorded in NHAIS within 6m of HPV positive
                                                                                                                                                                                                                                                                                                                                                                                                                                                                                                                                                                                                                                                                                                                                                                                                                                                                                                                                                                                                                                                                                                                                                                                                                                                                                                 |

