| To estimate the CIN2+ detection rate of self-sampling                     | Detection rates of disease (CIN2+) amongst women who return a self-sample                                                                    | Number of women with histologically confirmed CIN2+ (i.e. CIN2, CIN3 or invasive cervical cancer) in women who return a self-sample as a % of all women who return a self-sample (central laboratory data from the Cyres database)                                                                                                                                                                                                                                                                                                                                                                                                |
| To estimate the impact of self-sampling on colposcopy referral            | Rates of referral to colposcopy associated with self-sampling                                                                                | Number of colposcopy referrals as a % of all women who return a self-sample (from central laboratory Cyres)                                                                                                                                                                                                                                                                                                                                                                                                                                                                                                                       |
| To examine the uptake of self-sampling according to the mode of kit offer | Uptake of self-sampling kit within 6m after invitation when:
Sent kit directly (mail-out)

Vs

Offered kits opportunistically | Direct mail out: number of women returned self-sample as a % of total eligible sent kit directly (using data provided by NHAIS and mailing company)

Vs

Opportunistic: number of eligible women who returned a self-sample using opportunistic kit (data provided by NHAIS (sample "Source" field) as a % of total eligible women with Read codes for kits offered in GP records (GP record download)                                                                                                                                                                                                                |

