#### **6.2.4 Women who have opted out of NHS data usage via the National Opt-Out**

The national data opt-out was introduced on 25 May 2018 enabling patients to opt out of the use of their data for research or planning purposes. Women who have opted out of their NHS data usage via the national opt-out will be excluded from the study.

- For the mailout cohort, women who are documented in NHAIS to have formally opted out via the national opt-out will be removed from the data extract before the kits are posted.

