### **10.4.1 NHAIS dataset**

NHAIS holds the national cervical screening database and is therefore, the most accurate and complete source of screening data. GP records also contain cervical screening data, however, this tends to be less accurate than NHAIS as the two systems are not linked. As such, NHAIS data will be the main source of cervical screening data for the trial

Prior to each data extraction NHS Digital will apply the "exclusion" lists to remove women in the national data opt-out and women who have opted out from data usage for the study (see section 7.3.5). NHS Digital will then extract the data and, prior to sending it to KCL, will encrypt the NHS numbers (i.e. generate study ID) and convert the postcode to LSOA. In this way only anonymous line-level data will be provided to the trial team at King's for all eligible women (i.e. ≥6m overdue cervical screening) and therefore, will include data from women who have not consented to the trial. We will seek CAG approval for this. Data will include:

- Study ID (encrypted NHS number)
- Demographic data (age, LSOA (converted from postcode prior to sending to KCL))
- Cervical screening tests (including self-samples, cytology and HPV tests) dates and results, source of self-sample (opportunistic or mailout) including the last test before trial start, all tests during the trial period)
- Date identified for 15m mail out (if applicable)
- Cervical screening disclaimer returned (i.e. opted-out from the cervical screening programme)
- The woman's GP practice

These line-level NHAIS data will be linked to anonymised line-level data from GP records using the study ID to enable us to assess response rates and cervical screening activity according to ethnicity, whether or not women are offered kits in GP primary care.

We will also collect anonymous aggregate data:

- Practice-specific coverage at before study start, monthly and at the end of the trial

- An additional extract on practice-specific coverage may be requested after the trial has ended (after approximately 13 months after the last kit was handed out) to assess long term coverage.

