#### **10.4.4 GP record datasets**

Electronic GP record data will provide key data for the trial that are not available from the other data sources, such as ethnicity, granular details of the opportunistic offer (kits offered, accepted and declined, reasons for declining kits, and health professional type offering kits).

Cervical screening (dates and results) data will be obtained to enable us to assess how accurate GP records are for identifying women eligible for the opportunistic offer (it may be that kits may be offered to women who are  $\geq 6$ m according to their GP records but not in NHAIS. Also, cervical screening data in GP records may contain details of tests taken in other countries which are not recorded in NHAIS.

EMIS searches will be written to exclude women who are coded to have opted out from data usage for the study (see section 7.3.5).

GP record data will be extracted in bulk using EMIS searches that have been specially written for the trial. Extracts are likely to be downloaded from participating GP practices once they sign up to the trial (historical cohort data), at the end of the trial and depending on logistics, at several points during the study (e.g. on a monthly basis, at the end of active recruitment). These data extracts will be downloaded centrally at the CCG level by a member of the relevant CCG. If central download is

not possible, it will be carried out by each GP practice by a member of the practice team. The Clinical Effectiveness Group (CEG) have confirmed that they have centralised access to all GP practice data in Tower Hamlets and Newham CCG. Similarly, North East London Commissioning Support Unit (NEL CSU) have access to data from all GP practices in Barnet and Islington CCGs. Camden CCG have an IT lead who we plan to liaise with to extract data for Camden GP practices.

De-personalised line-level data will be collected for all women who are eligible (i.e.  $\geq 6m$  overdue cervical screening) and therefore, will include data from women who have not consented to the trial.

CAG approval will be sought to allow download of identifiable data at the CCG level and to allow the trial team at KCL to access de-personalised line-level data from women who have not consented to the trial. The CCG IT team will encrypt the NHS numbers before securely sending the data to King's.

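### The national data opt-out is filtered from NHAIS returns but not from GP-record offers, so opportunistic uptake in the mode-of-offer comparison is biased low

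*Protocol*

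**What the plan says.** All references are to the Protocol.

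- **Rule (6.2.4).** "Women who have opted out of their NHS data usage via the national opt-out will be excluded from the study". The one step listed under it concerns the postal pathway: "For the mailout cohort, women who are documented in NHAIS to have formally opted out via the national opt-out will be removed" before kits are posted. Sections 6.2.2 and 6.2.3, on disclaimer signers and HIV-positive women, each say how the opportunistic pathway treats the group. Section 6.2.4 does not.
- **Offer in primary care (6.2, 7.2.2).** The alert uses age, time since last test, and hysterectomy or cervical amputation codes. The exclusion criteria in 6.2 do not name the national opt-out, so the professional's eligibility check would not catch it.
- **NHAIS extract (10.4.1).** Before each extraction NHS Digital applies exclusion lists "to remove women in the national data opt-out and women who have opted out from data usage for the study".
- **GP-record extract (10.4.4).** "EMIS searches will be written to exclude women who are coded to have opted out from data usage for the study". The section cited for that code, 7.3.5, describes dissent from this trial recorded by the practice.
- **Laboratory and colposcopy data (10.4.2, 10.4.3).** Line-level data are supplied for women who return a self-sample. No opt-out filter is stated.
- **Endpoints (3.2).** For uptake by mode of offer, opportunistic returns come from NHAIS and the denominator is "total eligible women with Read codes for kits offered in GP records". Primary uptake takes returns from both NHAIS and the central laboratory. Follow-up counts HPV-positive women who "have a conventional cervical screening test recorded in NHAIS within 6m of HPV positive", while 7.8.1.1 names both NHAIS and GP records as sources.

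**The concern.** The two halves of one ratio pass through different filters. A national opt-out woman at a participating practice can be flagged, offered a kit and coded as offered, and her offer reaches the trial team through the GP-record extract. If she returns the kit, the NHAIS line holding her result is removed before the extract is sent. In the mode-of-offer endpoint she then counts as a non-responder.

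Mail-out women are filtered before posting, so they leave numerator and denominator together. The error therefore falls on one side of the comparison between the two ways of offering kits, which is a question the trial is meant to inform. Section 7.3.5 already recognises the principle for trial-specific opt-outs: because there are two data sources, it sets out two steps. For national opt-outs only the NHAIS step is written down.

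**Working it through.** **1. The plan's own base (9.1, 9.1.2).**

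- Eligible: 190,579 × 106/212 = 95,290 (stated about 95,000)
- Consulting: × 0.60 = 57,174 (stated 57,000)
- Offered: × 0.30 = 17,152 (stated 17,100, later 17,000)
- Accepting: × 0.70 = 12,006 (stated about 12,000)
- Returning: 17,152 × 0.50 = 8,576 (stated about 8,500)

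The base reproduces. The plan's rounded 8,500/17,000 = 50% is used below.

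**2. Observed uptake when only the numerator is filtered.** Let q be the share of women offered kits opportunistically who are national opt-outs. The protocol gives no value, so q is an assumption, shown from 0.5% to 10%. With equal return rates, observed uptake = 8,500(1 − q)/17,000 = 50% × (1 − q).

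| q | Opt-out offers in denominator | Returns missing from NHAIS | Observed uptake | Shortfall (points) |
|---|---|---|---|---|
| 0.5% | 85 | about 43 | 49.75% | 0.25 |
| 1% | 170 | 85 | 49.5% | 0.5 |
| 2% | 340 | 170 | 49.0% | 1.0 |
| 5% | 850 | 425 | 47.5% | 2.5 |
| 10% | 1,700 | 850 | 45.0% | 5.0 |

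The shortfall equals the ±1.0% precision stated in 9.1.2 when q = 0.01/0.50 = 2%.

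**3. If opt-out women return kits half as often (25%).** True uptake among all women offered is 50% × (1 − q) + 25% × q. At q = 5% this is 48.75%, against 47.5% observed. The missing returns cost 1.25 points, half the figure in the table. Against the population 6.2.4 leaves in the study, whose uptake is 50%, the gap is still 2.5 points, because the opt-out offers remain in the denominator.

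**4. One rule on both sides.** 8,500(1 − q)/[17,000(1 − q)] = 50% for any q.

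**5. Where else it could matter.**

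- *Primary uptake.* If returns are taken from NHAIS alone, step 2 applies to the opportunistic component. If laboratory returns are counted too, these women's returns are present and there is no such loss. The same woman could then be a returner in the primary endpoint and a non-returner in the mode-of-offer endpoint.
- *Follow-up.* Section 3.2 names no source for the HPV-positive denominator. If positives came from the laboratory and follow-up tests from NHAIS alone, the 85% attendance cited in 7.5.2 would read 85% × (1 − q): 84.2%, 83.3% and 80.8% at 1%, 2% and 5%, where q is now the opt-out share among the positives counted. If both come from NHAIS, or GP records supply the tests as 7.8.1.1 allows, this bias does not arise.

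**The case against.** The best defence is that the protocol never says these women are kept. The rule in 6.2.4 is not limited to one pathway, the list of EMIS exclusions in 10.4.4 is not said to be complete, and the denominator is restricted to eligible women, which could be read to leave out anyone excluded under 6.2.4. Section 10.4.1 also plans to link NHAIS and GP-record lines by study ID to assess response rates. If uptake is computed only on linked women, an opt-out woman with no NHAIS line leaves both counts and there is no bias. The opt-out rate is unknown, and at 0.5% to 1% the effect is 0.25 to 0.5 points.

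These points limit the concern but do not remove it. Section 10.4.1 names the national opt-out among its filters, whereas 10.4.4 names only the study-specific code. The endpoint as written divides an NHAIS count by a GP-record count, and nothing requires an NHAIS line for a woman to enter the denominator.

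A reader might infer that these women's returns and follow-up tests are lost to the trial and that the error is beyond repair. The documents do not support that. Primary uptake also draws on the laboratory, follow-up may draw on GP records, and colposcopy and histology reach the team through the laboratory's Cyres extract for all returners. Linkage by study ID (10.3, 10.4.1) would identify most affected returners: the laboratory checks eligibility (7.6.3.1) and does not test samples from women who are not overdue (7.5.4), so a tested sample with a GP offer code and no NHAIS line stands out.

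**Conclusion.** The concern holds for one secondary endpoint. The exclusion in 6.2.4 is carried out for the mail-out and the NHAIS extract but has no stated counterpart in the opportunistic alert or the GP-record extract. The mode-of-offer endpoint, computed as defined, therefore understates opportunistic uptake and leaves mail-out uptake untouched.

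With equal return rates the shortfall is 0.5, 1.0 and 2.5 points at assumed opt-out shares of 1%, 2% and 5%. Measured against all women offered, it is half that if opt-out women return kits half as often. The size rests on an opt-out share the protocol does not give, on opt-out women being offered kits, and on an unlinked GP-record denominator. Primary uptake and follow-up are affected only if NHAIS is the sole source of returns or follow-up tests while the offers or HPV positives come from an unfiltered source.

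**What to change.** 1. Put the numerator and denominator of the mode-of-offer endpoint under one rule. Either apply the national opt-out at GP-record extraction, so that 10.4.4 matches 10.4.1, or restrict the denominator to offered women who have a line in the filtered NHAIS extract. The second route also drops women who are overdue in GP records but not in NHAIS, so the text should say so.
2. Name one source of returns for the primary and mode-of-offer uptake endpoints, and count a return only for a woman in the denominator. Otherwise filtered offers combined with unfiltered laboratory returns would err the other way: at q = 2%, 8,500/16,660 = 51.0%.
3. Report the aggregate number of women removed under the national opt-out.
4. Reconcile 6.2, 6.2.4 and 7.2.2 on whether these women are offered kits opportunistically.

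The cost is a change to the search specification or one linkage condition, plus a few sentences. The downside is a slightly smaller opportunistic denominator. No change to the laboratory file or to the NHAIS filter is needed.

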## **7 TRIAL PROCEDURES**

### **7.1 Selection of GP practices**

Expression of Interest (EOI) forms will be sent to all 212 GP practices in the five CCGs. We anticipate there will be strong interest in participating and estimate that approximately 50% (~106) of GP practices will be willing to take part.

We will use a pragmatic and adaptive approach to recruit and set up GP practices in the trial. If substantially more GP practices than the anticipated 106 express interest in participating, we may select practices at random, stratifying based on the number of under-screened women in each practice, the active recruitment period remaining and available study resources.

#### **7.1.1 Early Adopter (flagship) GP practices**

A small cohort of early adopter GP practices will be identified as flagship practices with whom we already have established relationships with and/or who have taken part in our previous self-sampling studies. We will aim to have one in each of the five participating CCGs. The trial will start at these practices and they will help us generate lessons for the wider roll-out of the trial; including piloting and refining content and structure of the Site Initiation Visit. If we randomise the start date at each practice (as described in section 4.1.1 Randomisation) these practice would be excluded from the randomisation.

#### **7.1.2 GP training**

Participating GP practices will receive full training as part of the Site Initiation Visit (SIV). Given the large number (~106) of GP practices to set-up a pragmatic and strategic approach will be taken. For example, SIVs may be carried out by CCG area in batches using a mixture of communal training (GP or CCG training days, Primary Care Networks) and/or delivered by webinar (~40 minute) with a short test afterwards to check for understanding, delivered via a skype call or on-site training (depending on GP practice preferences).

The training will cover all practical and clinical aspects of the trial (how to offer self-sampling kits, clinical pathway, frequently asked questions by women, logistics of kit management at the practice, results management). A self-sampling webpage aimed at health professionals will be made available through the North Central and East London Cancer Alliance website. The web page will host a short training video about the trial including FAQs.

### **7.2 Participant identification**

#### **7.2.1 Direct mail-out**

Under a Section 251 exemption, eligible women will be identified using the national cervical screening database NHAIS (National Health Application and Infrastructure Services - owned by NHS England and PHE who are the data controllers for the cervical screening database). Accessing these data is the most accurate way of identifying eligible women and ensuring that the women invited to the trial are the appropriate population (i.e. women from a participating GP practice).

Once each GP practice has received training as detailed in section 7.1.2; the study team will issue confirmation for the GP practice to be included in the monthly mailout.

At the start of each month, the study team will then provide NHAIS with a table of participating GP practices. Following receipt of this table; a list of women (from participating GP practices) who reach the 15-month anniversary of their last test due date without being screened (by self-sample or

conventional cervical screening (HPV primary testing or cytology) will be extracted from NHAIS. This 15-month timepoint has been chosen as an approximate midpoint between the usual call/recall screening invitation and reminder letters. This is to make it obvious to women that the self-sampling offer is different from the usual screening invitation and also to avoid overwhelming women with letters about screening. Other than this, the 15-month timepoint is arbitrary, and could equally be taken at a similar timepoint (e.g. 18 months).

**Figure 1 Timeline of call/recall letters and study direct mail-out of kits**

[figure not shown]

The NHAIS extract will include the women's:

- Full name
- Date of Birth
- Address including postcode
- NHS number
- GP Practice Code

These are the minimum fields required to ensure that kits can be sent to the correct women's homes identified at the lab and that the results can be accurately reported to the correct women and correct GP practice.

NHS Digital will make the list of eligible women from current participating GP Practices in NHAIS available to the Cervical Screening Administration Service (CSAS) who are responsible for sending invitations and reminders for the call/recall Cervical Screening Programme in England (see Figure 2 for further details). CSAS will then send the list to a commercial print company (contracted by UCL and/or KCL) with the appropriate level of information governance standards to securely handle NHS data (i.e. with International Organisation for Standards (ISO) accreditations and Information Governance (IG) approved on the NHS IG tool kit, their Data Security and Protection Toolkit will be compliant with NHS Digital Data Security and Protection regulations).

The print company will send a pre-notification letter to women (on behalf of the GP practices and the Cervical Screening Programme) informing them that they are overdue cervical screening and that a self-sampling kit will be posted to them. It has been hypothesised that sending a pre-notification letter enhances self-sampling uptake. Within 1-2 weeks of sending the letter, the print company will send women a self-sampling kit along with an invitation letter.

GP endorsement may be included on the pre-notification and/or invitation letters as this has been shown to increase participation in colorectal screening (and would be cost neutral).

Self-sampling kits in the mail-out arm will comprise:

- A CE-marked dry flocked swab (552C.80 Copan FLOQswab™) in a tube with a re-sealable lid
- Pictorial and written instructions for self-collecting the vaginal sample
- A UN3373-compliant freepost envelope (padded or polybag) or box that is pre-addressed to the laboratory

- A patient information booklet
- A specimen bag
- A lab request/consent form
- A questionnaire (questionnaire-based sub-study)

Women will be instructed to write the date sample taken on the tube label and lab request/consent form. Women will collect their self-sample at home and post it directly to the laboratory (Royal Mail freepost in line with Packaging Instruction P650 for biological substances classified as UN3373) for analysis.

